### Data analysis

Baseline characteristics in both arms will be compared to check if randomisation has resulted in an equal distribution of the main outcome measures, prognostic factors and known confounding factors such as age, gender, living status and educational level.

The primary analysis will be an intention-to-treat analysis. All continuous responses will be analysed in a linear mixed model with responses at baseline and 3, 6, 9, 12 and 26 weeks. If necessary, missing items within a questionnaire will be imputed using multiple imputation techniques. In these analyses we will take into account the levels of neurosurgeon, primary care therapists, patient and time of measurement. The effect of interest for the present study will be the time by treatment interaction. Therefore, regression coefficients with 95% confidence intervals (CI) between baseline and follow up measurements will be calculated. If appropriate, analyses will be adjusted for patient characteristics that differ between the two groups. For the dichotomous outcomes we will use a generalised mixed model (logit link) with the same multilevel structure, and the effect of interest will be the difference between groups at each time point. Odds ratios with 95% CI between intervention and control groups will be calculated.

A per protocol analysis will be performed to estimate the extent to which protocol deviations may bias the results. A protocol deviation is defined as receiving one or more sessions of exercise therapy in the first six to eight weeks after surgery in the control group, or not receiving any sessions of exercise therapy in the first six to eight weeks postoperatively by participants in the intervention group.

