### Sample size

Power calculations were based on a Cochrane review assessing the effectiveness of rehabilitation following lumbar disc surgery
[18] and were performed for the three main outcomes (for all: power 0.9; alpha 0.05). To detect a clinical relevant mean difference in a multi-level analysis between the continued rehabilitation group and the watchful waiting group of 8 points on the ODI (SD 15), a total of 165 patients is needed. To detect a difference of 2 points (SD 3) for pain (11-point NRS) a total of 105 patients is needed. For detecting a 20% difference on the dichotomised global perceived recovery (recovered vs not recovered) a total of 150 patients is needed. Anticipating 15% potential study withdrawal, a total of 200 patients will be recruited. Participants will be unequally distributed (109 intervention vs. 91 control) to allow for multilevel analysis, taking into account the multilevel structure of the data in the intervention group.

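### Continuous outcomes: as worded, the treatment effect is a difference in change from baseline; using the baseline score as an adjustment would be more precise at no cost

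*Protocol article*

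**What the plan says.** All references are to the protocol article.

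- **Data analysis, model:** "All continuous responses will be analysed in a linear mixed model with responses at baseline and 3, 6, 9, 12 and 26 weeks". Baseline is therefore one of the responses.
- **Data analysis, effect:** "The effect of interest for the present study will be the time by treatment interaction".
- **Data analysis, estimate:** "regression coefficients with 95% confidence intervals (CI) between baseline and follow up measurements will be calculated".
- **Data analysis, adjustment:** adjustment is foreseen only where appropriate, for patient characteristics found to differ between the groups. The baseline value of the outcome is not named as a covariate, and nothing says that the arms share a common baseline mean.
- **Data analysis, dichotomous outcomes:** here the effect is the group difference at each time point, not an interaction.
- **Sample size:** the calculations "were performed for the three main outcomes (for all: power 0.9; alpha 0.05"). The ODI requirement is "8 points on the ODI (SD 15), a total of 165 patients is needed". For pain: "To detect a difference of 2 points (SD 3) for pain (11-point NRS) a total of 105 patients is needed". The contrast is described as a mean difference between groups. No pre/post correlation is given, and the SD is not identified as that of a score or of a change.

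**The concern.** In a model with arm, time and their interaction, and with baseline as one of the occasions, each interaction coefficient is the difference between arms in change from baseline. Such an estimate carries the full noise of the baseline measurement. An analysis that uses baseline as a predictor, or that builds in the equality of the arms which randomisation guarantees in expectation, removes noise instead of adding it.

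Baseline is taken hours to days before surgery and every follow-up comes after it, so the correlation between the two need not be high. Two things are at stake: the width of the confidence intervals for the continuous outcomes, and whether the ODI calculation, made for a plain mean difference, still describes the power of the analysis that will be run.

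**Working it through.** **Inputs.** From Sample size: ODI difference 8, SD 15, N 165; pain difference 2, SD 3, N 105; alpha 0.05 (taken as two-sided), power 0.90; 200 recruited with 15% withdrawal, so 200 × 0.85 = 170 evaluable; allocation 109:91, so 170 splits as 92.65 and 77.35. Assumed, because the article does not give it: r, shown from 0.2 to 0.6.

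**1. The plan's own figures.** N = 4 × (1.960 + 1.282)² × SD²/difference² at 1:1.
- ODI: 147.8 at 1:1, 149.0 at 109:91, against 165 stated. Ratios 1.117 and 1.108.
- Pain: 94.6 at 1:1, 95.3 at 109:91, against 105 stated. Ratios 1.110 and 1.101.

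The printed inputs alone do not return 165 or 105. One undisclosed inflation of about 1.11 explains both, and the text refers to a multilevel analysis, so this is not counted as an error. Results below are given without clustering loss and with the implied inflation (ODI 1.108, pain 1.101).

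**2. Variances relative to a single follow-up comparison, equal SDs.**
- Difference in change: 2(1 − r).
- Baseline-adjusted: 1 − r².
- Ratio: 2(1 − r)/(1 − r²) = 2/(1 + r), which is 1.54 at r = 0.3, 1.33 at 0.5 and 1.18 at 0.7.

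With unequal SDs (SD0 before, SD1 after) the excess variance of the change analysis is (SD0 − r·SD1)², which is never negative.

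**3. Check in the mixed model itself.** Generalised least-squares standard errors for six occasions, 93 against 77 patients, SD 15:

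| r | baseline means free | baseline means constrained equal |
|---|---|---|
| 0.3 | 2.735 | 2.205 |
| 0.5 | 2.311 | 2.002 |
| 0.7 | 1.790 | 1.650 |

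The first column equals the change-score formula and the second the covariate-adjusted formula. A comparison of follow-up scores alone has SE 2.311.

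**4. ODI power at 170 evaluable, one visit.** The SE of a follow-up comparison is 15 × √(1/92.65 + 1/77.35) = 2.310 without clustering loss, and 2.310 × √1.108 = 2.431 with the implied inflation. Power is Φ(8/SE − 1.96), with the SE multiplied by the square root of the factor in step 2.

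| r | change, no loss | change, inflated | adjusted, no loss | adjusted, inflated |
|---|---|---|---|---|
| 0.2 | 0.78 | 0.74 | 0.94 | 0.92 |
| 0.3 | 0.83 | 0.79 | 0.95 | 0.93 |
| 0.4 | 0.89 | 0.85 | 0.97 | 0.95 |
| 0.5 | 0.93 | 0.91 | 0.98 | 0.97 |
| 0.6 | 0.97 | 0.96 | 0.99 | 0.98 |

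Ninety per cent needs an SE of 8/3.242 = 2.468. The change analysis reaches that at r = 1 − (2.468/2.310)²/2 = 0.43 without loss, and at 1 − (2.468/2.431)²/2 = 0.485 with it. A different assumption, a design effect of 1.2 in the intervention arm only, gives 0.80 against 0.94 at r = 0.3.

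**5. Pain at 170 evaluable.** The same calculation with 2 and 3 puts the 90% threshold at r = 0.11 without loss and 0.19 with it.

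**6. How far the ODI threshold moves.** The change analysis matches a follow-up comparison at r = SD0/(2·SD1): 0.5 for equal SDs, 0.4 to 0.6 for SD ratios of 0.8 to 1.2. If the five follow-ups are averaged, with correlations of 0.5 to 0.8 among them, the corresponding value is 0.30 to 0.42. If SD 15 is already the SD of a change, planned power stands at any r.

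**The case against.** The strongest defence is that free baseline means are inferred, not stated. A model that constrains the arms to be equal at baseline also has baseline as a response and the interaction as its effect, and step 3 shows that it is fully efficient. A condensed article may leave that parameterisation to the analysis plan. This stands in part: the text is compatible with the better model. But the article itself names the effect and the baseline-to-follow-up contrast, and its only adjustment depends on observed imbalance, so a reader would not arrive at the constrained model from the text.

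Several stronger readings are tempting and are not supported.

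- **That the trial is underpowered.** This needs a low r, SD 15 as a score SD, similar SDs before and after surgery, and a single-visit test. The article gives none of these.
- **That power on pain is lost.** Precision is lost, but pain needs 105 patients and 170 are expected to be evaluable.
- **That global perceived recovery is affected.** It is compared between groups at each time point, with no baseline value.
- **That the false-positive rate is inflated.** The article lists levels, including patient and time of measurement, but no covariance structure. A random patient intercept alone would understate the SE if baseline correlated less with follow-up than the follow-ups did with each other. With assumed correlations of 0.3 and 0.6, the fitted average is (5 × 0.3 + 10 × 0.6)/15 = 0.5, so the modelled variance is 1.0 against a true 1.4, and a nominal 5% test rejects 9.8% of the time. That is a reason for care, not a property of the stated plan.
- **That the estimate is biased.** Under randomisation the difference in change is unbiased; a chance baseline imbalance only adds noise.

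**Conclusion.** This is a free improvement rather than an error that invalidates the analysis. On the natural reading, the planned estimate for the ODI, pain and the other continuous outcomes is valid but less precise than a baseline-adjusted one at any realistic correlation; only the size of the loss depends on r. For equal SDs the excess variance is 54% at r = 0.3 and 33% at r = 0.5.

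A fall in ODI power below the planned 90% is possible, and would occur for r under about 0.43 to 0.485 on the conditions in steps 4 and 6, but it is not demonstrated. The precision result rests on randomisation and on the reading that baseline means are left free; the power result rests on those further conditions as well.

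**What to change.** In Data analysis, replace the description of the effect for continuous outcomes with one of two equivalent choices:

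1. Keep baseline as a response but constrain the arm means to be equal there, with no treatment main effect at baseline.
2. Use the 3 to 26 week scores as responses, with categorical time, arm, arm by time, and the baseline score by time as fixed effects.

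In either case, report the adjusted between-arm difference with its 95% CI at each follow-up. As a precaution, specify an unstructured covariance over time within patient.

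The cost is about two sentences. Baseline scores for these outcomes are already collected, and no increase in sample size is needed. The choice should be fixed before outcome data are examined, since the Blinding section says that the researcher and statistician cannot be blinded.

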### Treatment allocation

To conceal treatment allocation, randomisation lists per hospital will be generated by computer prior to study commencement by an independent person. To achieve the predetermined size of treatment and control group, weighted block randomisation (blocks of four) will be used. Directly after having received the completed baseline questionnaire, the research nurse will open the next consecutive a priori prepared numbered opaque envelope containing the assigned postoperative strategy. Patients allocated to the intervention group will receive a list of the participating therapists and are asked to make an appointment for the first treatment session in the first week after surgery. Within one week post-surgery the research nurse will contact the patient to ensure that an appointment has been made and to record the date of the first appointment.

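### Covariates are to be chosen by observed baseline imbalance, on undefined criteria and by an unblinded statistician; a short prognostic set including hospital should be fixed instead

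*Protocol article*

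**What the plan says.** The Data analysis section opens with a comparison of the arms: "Baseline characteristics in both arms will be compared to check if randomisation has resulted in an equal distribution of the main outcome measures", and of prognostic factors and "known confounding factors such as age, gender, living status and educational level". Later in the same section comes the rule that uses it: "If appropriate, analyses will be adjusted for patient characteristics that differ between the two groups". No threshold, test or closed list is attached to either sentence.

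On the model, the section says: "In these analyses we will take into account the levels of neurosurgeon, primary care therapists, patient and time of measurement". For continuous outcomes the baseline value is one of the responses, and the effect of interest is the interaction of time with treatment. For dichotomous outcomes it is the group difference at each time point, as an odds ratio from a logit mixed model with the same levels.

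Three other places bear on this:
- Treatment allocation: "randomisation lists per hospital will be generated by computer prior to study commencement by an independent person", and "weighted block randomisation (blocks of four) will be used". Hospital is therefore the stratum.
- Prognostic factors: length and severity of complaints before surgery and psychosocial factors are named as predictors of poor outcome.
- Blinding: the unequal arm sizes are said to rule out blinding of the researcher and the statistician who analyse outcomes.

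**The concern.** In a properly randomised trial any baseline difference is chance. Comparing the arms does not show whether randomisation worked, and an observed difference does not make a variable a confounder that needs adjustment. What justifies adjustment is that a variable predicts the outcome, and that is known before the trial starts. The article names such variables, but under its rule they enter the model only if they happen to be unbalanced.

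The rule also leaves the model open until the data can be seen by arm. Two undefined conditions and an open-ended candidate list, applied by someone who knows the allocation, allow the adjusted or the unadjusted result to be presented as the main one. This is a stated rule and not a detail left out. A fixed covariate list in an analysis plan that is not shown would contradict it rather than fill it in.

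A smaller matter is that the stratification variable, hospital, is not among the listed levels.

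**Working it through.** The plan gives no figure for covariate adjustment, so there is none to reproduce. The checks use its sample-size inputs and stated assumptions.

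**1. False-positive rate and power, single time point.**
- Inputs from Sample size: 109 and 91 patients, 15% withdrawal, 8 ODI points, SD 15. Analysed: 109 × 0.85 ≈ 93 and 91 × 0.85 ≈ 77. Effect: 8/15 = 0.533 SD.
- Assumed: one baseline covariate with correlation 0.3, 0.5 or 0.7 with the outcome; two-sided 5%.
- Simulated with 10,000 trials under the null and 5,000 under the effect.

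| | r = 0.3 | r = 0.5 | r = 0.7 |
|---|---|---|---|
| Null: adjust only if baseline p < 0.05 | 0.044 | 0.046 | 0.039 |
| Null: covariate fixed in advance | 0.047 | 0.053 | 0.050 |
| Null: more favourable of adjusted and unadjusted | 0.058 | 0.076 | 0.084 |
| Power: adjust only if baseline p < 0.05 | 0.933 | 0.938 | 0.945 |
| Power: covariate fixed in advance | 0.954 | 0.977 | 0.997 |

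The simulation error of a null rate near 0.05 is √(0.05 × 0.95/10,000) = 0.002. A mechanical rule does not inflate; free choice does. The power gap is 2 to 5 percentage points, but only for a comparison that does not already use the baseline outcome.

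**2. Continuous outcomes under the planned model.** The effect compares y(follow-up) − y(baseline) between arms. A time-constant covariate with effect β adds βx to both terms and cancels. A simulation with 93 and 77 patients, six time points, a random patient intercept and a covariate explaining about one third of the variance (both assumed) confirms it:
- Complete data: the interaction estimate is the same with and without the covariate (largest difference 8 × 10⁻¹⁴), with SE 0.1523 both ways.
- 15% of follow-up values missing at random: SE 0.1607 without and 0.1605 with.

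The power gap in step 1 therefore does not carry over to these outcomes.

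**3. Global perceived recovery.** Table 1 shows no baseline measurement, so no change from baseline cancels the covariate. An odds ratio can also shift when a balanced prognostic covariate is added. Illustration with assumed figures: two equal strata, odds ratio 3 in each.
- Control recovery 40% and 80%: odds 0.667 and 4 become 2 and 12, so recovery is 66.7% and 92.3%. Overall 60% against 79.5%, odds ratio (0.795/0.205)/1.5 = 2.58.
- Control recovery 55% and 65%: odds 1.222 and 1.857 become 3.667 and 5.571, so recovery is 78.6% and 84.8%. Overall 60% against 81.7%, odds ratio 2.97.

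So 3 within strata is 2.58 to 2.97 overall, without any imbalance.

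**4. Hospital.** Assumed: 10 hospitals (Setting) of 17 patients, three surgeons in each, 1:1 blocks of four as a simplification, variance components known. SE in outcome-SD units:

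| Hospital + surgeon variance share | Surgeon level only | Surgeon and hospital | Ratio |
|---|---|---|---|
| 0.02 + 0.02 | 0.1521 | 0.1513 | 1.005 |
| 0.05 + 0.03 | 0.1502 | 0.1486 | 1.011 |
| 0.10 + 0.02 | 0.1478 | 0.1450 | 1.019 |

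Null rejection with the surgeon level only was 0.044, 0.049 and 0.042, so there is no inflation.

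**The case against.** The strongest reply is that covariate lists and stratum terms usually belong in the analysis plan, that the continuous outcomes hardly react to the choice, and that no error inflation follows from the rule itself. Much of this stands. Steps 1 and 2 confirm the last two parts, and the absence of a full covariate list would not be a finding. What remains is the imbalance rule, which the article does state.

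Several stronger readings are tempting, and the document does not support them:
- *The nominal error rate is lost.* This needs an analyst who takes the better of two results. The wording allows that but does not plan it.
- *A chance difference is likely, so adjustment is likely.* With independent checks at 5%, at least one of four differs in 1 − 0.95⁴ = 18.5% of trials, and one of eight in 33.7%. The article states no test or threshold, and the chance of an imbalance is not an error rate.
- *Adjustment would save a share of the sample equal to the explained variance.* That formula is for a linear comparison at one time point. It fails for a time-by-treatment contrast with baseline as a response. It also fails for a logit model, where in one simulation the SE of the log odds ratio rose from 0.33 to 0.36 with a prognostic covariate, although power can still improve.
- *Hospital differences leak into the treatment effect.* This would need allocation shares that differ between hospitals. Blocks of four cannot each give 109:91, so it is possible, but block composition is not given and no size can be put on it.

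One limit applies to step 3. The planned logit model has a patient level, so its odds ratio already conditions on a patient effect. The better that effect is modelled, the smaller the shift from adding a covariate.

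**Conclusion.** The concern holds in a limited form. The article fixes a poor rule: adjustment depends on observed imbalance, the criteria are undefined, and the statistician is unblinded. If the freedom were used to pick the better result, false positives would rise from 0.05 to about 0.06 to 0.08, given one covariate correlated 0.3 to 0.7 with the outcome at a single time point. Applied mechanically, the rule inflates nothing.

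Global perceived recovery is most exposed, because it has no baseline value and the covariate set can change what its odds ratio describes. For ODI and pain the consequence is small under the planned contrast, assuming a random patient intercept and covariates entered as main effects only. The missing hospital term is a minor correction, with an SE 0.5% to 1.9% wider. That figure assumes that each surgeon works in one hospital, which the article does not say, and rests on assumed variance shares.

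**What to change.** - Delete the clause on adjusting for characteristics that differ. Before anyone sees outcomes by arm, fix one short covariate set and use it whatever the balance: hospital (fixed effect, or a level above neurosurgeon), age, gender, and length and severity of complaints before surgery, with the measure of severity named.
- For continuous outcomes, keep the baseline value either as a response, as now, or as a covariate, but not both. If precision is wanted there, enter the covariates with time interactions, since main effects alone gain almost nothing.
- For global perceived recovery, use the same set without a baseline-outcome term, and state that the odds ratio is conditional on it.
- Present the baseline table descriptively, not as a check on randomisation.

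The cost is wording and a few degrees of freedom: as fixed main effects, 9 for ten hospitals and about 4 for the other covariates, against some 170 analysed patients. Time interactions would add more. All the variables are already collected.

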#### Control group: watchful waiting policy

Participants assigned to the control group will not receive exercise therapy immediately after discharge from hospital. Patients may consult their neurosurgeon or general practitioner in case of recurring or increasing complaints, but no exercise therapy or other allied health care intervention will be initiated. The research nurses will limit the extent to which they will provide advice in case they will be called by patients allocated to the control group. To prevent diminishing contrast between groups, only advice that has been given during the clinical phase will be repeated.

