***Economic evaluation***								
Absence from work (PRODISQ)					X		X	X
Cost questionnaire					X		X	X

ODI: Oswestry Disability Index; NRS: Numerical Rating Scale; GPE: Global Perceived Effect Scale; SF-12: Medical Outcome Study Short Form 12; EQ-D5: EuroQol; ÖMPSQ: Örebro Musculoskeletal Pain Screening Questionnaire; FABQ: Fear-Avoidance Beliefs Questionnaire; CEQ: credibility/expectancy questionnaire; PCI: Pain Coping Inventory; PRODISQ: Productivity and Disease Questionnaire; wk: week or weeks.

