#### Primary outcome measures

The recommended core set of outcomes for low back pain research
[22] will be used, and all measures are self-reported.

Functional status will be assessed by the Oswestry Disability Index (ODI)
[23,24]. The ODI consists of 10 questions assessing aspects of daily living, each being scored on a six-point scale, ranging from 0–5. The total score comprises the 10 item-scores and ranges from 0 (no difficulty) to 50 (maximal difficulty).

Pain intensity will be measured for leg pain and low back pain on an 11-point numerical rating scale (0 = no pain to 10 = worst imaginable pain)
[25,26]. Average pain intensity over the preceding week will be measured, for leg pain and low back pain separately. At three days postoperative the pain at the time of measurement will be assessed, again for leg and back pain separately.

Global perceived recovery will be evaluated with the seven-point Global Perceived Effect scale (GPE), ranging from “completely recovered” to “worse than ever”
[22]. This will be dichotomised into success (completely and much recovered) and non-success (slightly recovered, no change, slightly worse, much worse and worse than ever).

The Medical Outcome Study Short Form 12 (SF-12) will be used to assess general health status
[27,28]. The 12 items cover the dimensions physical function and mental health. Sum-scales can be derived with scores ranging from 0–100 per dimension. Higher scores reflect better health.

The EuroQol (EQ-D5) will be administered to assess health related quality of life
[29,30]. This instrument evaluates 5 dimensions of quality of life on a three-point scale (no problems, moderate problems and severe problems). Utilities based on the EQ-5D will be estimated using the Dutch valuation tariff
[31].

Costs will be measured from a societal perspective using cost questionnaires. Only costs related to leg and back pain are considered and will include costs of continued rehabilitation, other health care costs, patient and family costs, and missed days of unpaid work. The cost questionnaires and the therapists’ registrations of sessions completed are also used to check compliance to the allocated treatment and possible cross-over, i.e. receiving exercise therapy in the control group either by means of direct access or referral.

A modified version of the Productivity and Disease Questionnaire (PRODISQ) will be used to evaluate absence from paid work

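### The per-protocol analysis cannot estimate the bias from protocol deviations: excluding patients on exercise therapy received after randomisation mixes selection with the effect of the deviations, and its time window is not fixed

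*Protocol article*

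**What the plan says.** - **Role and purpose** (protocol, Data analysis). "The primary analysis will be an intention-to-treat analysis". The section then adds: "A per protocol analysis will be performed to estimate the extent to which protocol deviations may bias the results".
- **Definition of a deviation** (same section). In the control arm it is "receiving one or more sessions of exercise therapy in the first six to eight weeks after surgery in the control group". In the intervention arm it is "not receiving any sessions of exercise therapy in the first six to eight weeks postoperatively by participants in the intervention group". The section does not say outright that deviators are excluded, and it names no adjustment for the reasons behind a deviation.
- **Why controls may seek care** (Control group: watchful waiting policy). "Patients may consult their neurosurgeon or general practitioner in case of recurring or increasing complaints", although the policy is that no exercise therapy is started.
- **Data sources** (Primary outcome measures). The cost questionnaires and the therapists' session records are both used to check compliance and "possible cross-over, i.e. receiving exercise therapy in the control group either by means of direct access or referral".
- **Timing** (Table 1). The row "Cost questionnaire" is marked at 6, 12 and 26 weeks only.
- **The six-to-eight-week period.** The Intervention group section describes it as the time until the patient next sees the neurosurgeon, with a length that depends on the hospital. The Follow-up consult section counts that consult from discharge, and leaves further treatment after it to the neurosurgeon.

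**The concern.** Both definitions of a deviation rest on what patients do after randomisation. The protocol's own text makes it plausible that controls cross over because of symptoms: they may see a doctor when complaints recur or increase, and they can reach exercise therapy by referral or directly. If those controls are left out, the remaining controls are a selected group and are no longer comparable with the intervention arm by design.

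The gap between the per-protocol and intention-to-treat results then has two parts that cannot be separated: removal of dilution by treated controls, and selection. A small gap would not show that deviations did little harm, and a large one would not show that they did much. The stated purpose invites both readings.

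The lesser problem is the window. If its end varies between hospitals and its origin is not the same throughout, the same control session can count as a deviation for one patient and not for another.

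**Working it through.** The protocol gives no figure for cross-over or for the per-protocol result, so there is nothing of its own to reproduce. The steps below show what the gap between the two analyses contains.

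**Inputs.** From the Sample size section: ODI SD 15 and target difference 8. Assumed, because the documents do not give them: a fraction q of controls crosses over, namely the worst q on a latent trait that has correlation ρ with ODI; everyone in the intervention arm attends.

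**Step 1: exercise has no effect.** Deviations then cannot bias anything, and intention-to-treat correctly gives zero. Leaving out the worst q of controls improves the retained control mean by s = SD × ρ × φ(c)/(1 − q), where c is the standard normal quantile at 1 − q. For q = 0.10 and ρ = 0.3: c = 1.28, φ(c) = 0.1755, so s = 15 × 0.3 × 0.1755/0.90 = 0.88 points.

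| q | ρ = 0.1 | ρ = 0.3 | ρ = 0.5 |
|---|---|---|---|
| 0.05 | 0.16 | 0.49 | 0.81 |
| 0.10 | 0.29 | 0.88 | 1.46 |
| 0.20 | 0.52 | 1.57 | 2.62 |
| 0.30 | 0.75 | 2.24 | 3.73 |

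The whole of each figure is created by the exclusion.

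**Step 2: exercise has the planned effect of 8 points, and controls who cross over gain all of it.** Intention-to-treat gives 8(1 − q), so dilution is 8q. Per protocol gives 8 − s. The gap, per protocol minus intention-to-treat, is 8q − s.

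| q | dilution 8q | gap, ρ = 0.1 | gap, ρ = 0.3 | gap, ρ = 0.5 |
|---|---|---|---|---|
| 0.05 | 0.40 | +0.24 | −0.09 | −0.41 |
| 0.10 | 0.80 | +0.51 | −0.08 | −0.66 |
| 0.20 | 1.60 | +1.08 | +0.03 | −1.02 |
| 0.30 | 2.40 | +1.65 | +0.16 | −1.33 |

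In no cell does the gap equal the dilution. At ρ = 0.3 it is near zero while dilution runs from 0.40 to 2.40 points, and its sign changes with ρ.

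**Step 3: recovery scale, also on assumed inputs.** With control recovery of 60%, a cross-over fraction x and recovery r among those who cross over, the remaining controls recover in (0.60 − x·r)/(1 − x). For x = 0.1, r = 0.4: 0.56/0.90 = 62.2%. For x = 0.2, r = 0.2: 0.56/0.80 = 70.0%. That is a shift of about 2 to 10 percentage points against the planned difference of 20.

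**Step 4: the window.**
- Length: fixed by the hospital's consult schedule (Intervention group section), but written only as a range in the deviation definition.
- Origin: surgery in Data analysis, discharge in Follow-up consult.
- Recording: the 6-week cost questionnaire can cover weeks 0 to 6. A control session between week 6 and a later consult first appears in the 12-week form, possibly alongside treatment permitted after the consult. The session forms come from participating therapists and may miss controls treated elsewhere.

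**The case against.** Intention-to-treat is primary, so the main conclusion does not depend on this analysis. Exclusion of deviators is inferred from the term, and an analysis plan that is not shown could add adjustment. Both points stand and limit the importance of the matter, but neither rescues the purpose that the protocol states.

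Three stronger readings are tempting and are not supported.

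- **That the per-protocol result must be biased against rehabilitation.** Symptom-driven cross-over pushes that way, but custom or preference could also drive it, and removing treated controls removes dilution, which pushes the other way. In the intervention arm, a deviator has attended no session at all. The first session is due in the first week after surgery, and patients who recover may stop early, having already attended. Nothing shows that never-attenders are the quickly recovered; they could equally be patients with complications.
- **That the window cannot be read from the data.** Therapist registrations are a second source. With a form per session and a recorded first appointment, attendance in the intervention arm can be settled. For controls, only the stretch from week 6 to a later consult is in doubt, and the questionnaire, which is not shown, may ask for dates.
- **That a control referred at a 6-week consult and treated in week 7 is counted as a deviator.** If the window closes at each hospital's own consult, as the Intervention group section suggests, that patient falls outside it. The definition in Data analysis does not say so, which is a reason to state it, not proof of misclassification.

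**Conclusion.** The point holds for the stated purpose. Exclusion on post-randomisation receipt of exercise therapy gives a comparison open to selection, and its distance from intention-to-treat is not an estimate of bias from deviations. This rests on the usual meaning of per protocol and on the plausibility, from the protocol's own text, of symptom-driven cross-over.

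Size and net direction are not known from the documents. The 0.16 to 3.73 ODI points and the 2 to 10 percentage points illustrate selection in the control arm alone, on assumed rates; a reader should not take them as estimates for this trial.

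The window is a lesser defect: its length varies by hospital, its origin is not uniform across sections, and control sessions after week 6 are dated less surely than earlier ones. The primary analysis is untouched, but the change is worth making because the protocol itself expects cross-over.

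**What to change.** 1. Keep intention-to-treat as the primary analysis.
2. Add a complier average causal effect estimate with allocation as the instrument. In the Step 2 example with q = 0.10, intention-to-treat gives 7.2, and dividing by the difference in receipt gives 7.2/(1 − 0.10) = 8, the effect assumed.
3. Define treatment received from the therapist registrations and cost questionnaires over one stated analysis window with one origin, after reconciling the Intervention group, Follow-up consult and Data analysis sections. A six-week window matching the 6-week cost questionnaire is the one the data support most directly. It would miss control sessions between week 6 and a later consult, so repeat the analysis with the hospital's own consult date as the end. This concerns the analysis only, not when patients are seen or treated.
4. If the per-protocol analysis is kept, call it a sensitivity analysis open to selection and delete the statement that it estimates bias.

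The cost is wording and an additional model on data already planned, though repeated measures, a binary outcome and the neurosurgeon and therapist levels make that model more than routine. The interval will be wider. The exclusion restriction, that allocation acts only through the sessions received, must be stated as an assumption: patients are not blinded and outcomes are self-reported (Blinding section), so it is open to doubt.
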